### Measurements

Measurements for primary and secondary endpoints will take place at baseline, 6 and 12 months (end of the intervention).

#### Primary Study Endpoints

##### Whole Body, Hip and Spine Bone Mineral Density, and Body Composition

BMD (g/cm^2^) of the hip (total hip) and lumbar spine (L_2–4_) regions as well as whole body bone mineral content (BMC, g) will be assessed by dual-energy X-ray absorptiometry (DXA, Hologic Discovery A, Waltham, MA). The Instant Vertebral Assessment (IVA) and Quantitative Morphometry (QM) program will be used to determine the presence or absence of vertebral fractures prior to initiation of the study. In addition, regional and whole body lean mass (including appendicular skeletal muscle mass) and fat mass will be derived from the whole body scan. Measurement of trunk adiposity is an important measure of chronic disease risk, and will be assessed from trunk fat mass obtained from the whole body scan and the ratios of trunk fat to limb fat, and trunk fat to total fat. In addition, upper and lower limb and trunk muscle tissue will be measured to evaluate region specific changes in muscle hypertrophy or atrophy.

##### Cardiorespiratory Capacity

Maximum oxygen uptake (measure of aerobic capacity) will be measured by expired air analysis during a staged walking test on a motorized treadmill. Exercise capacity (in multiples of resting metabolic rate termed Metabolic Equivalent of Task – METS) will be determined on the basis of the speed and grade of the treadmill as well as direct expired air gas analysis. Electrocardiogram will be recorded using a 12-lead monitoring system and blood pressure will be measured each testing minute by sphygmomanometer.

##### Blood Pressure and Arterial Stiffness

A validated oscillometric device (HEM-705CP, Omron Corporation, Japan) will be used to record brachial BP at the dominant arm in triplicate. Central (ascending aortic) BP and indices of arterial stiffness will be determined by pulse wave analysis using SphygmoCor version 6.1 software (AtCor Medical, Sydney, Australia). Radial artery pressure waveforms will be captured at the right arm by applanation tonometry using a high fidelity micromanometer (SPC-301, Millar Instruments, Houston, Texas, USA). A generalised transfer function is applied to the radial artery waveform in order to obtain the pressure waveform at the ascending aorta. This method has been validated against invasive techniques for determination of central BP and the augmentation index (AIx) is a marker of systemic arterial stiffness.

##### Blood Markers

Testosterone, prostate specific antigen (PSA), insulin, lipid profile, glucose, HbA_1c_, alkaline phosphatase, Pro collagen Type 1 N-Terminal Propeptide (PINP), and C- reactive protein (CRP) levels will be measured commercially by an accredited Australian National Association of Testing Authorities (NATA) laboratory (Pathwest Diagnostics, Perth, Western Australia).

#### Secondary Study Endpoints

##### Muscle Strength and Endurance

Prior to muscle testing, subjects will be familiarized to all assessment procedures. In addition, a warm-up consisting of aerobic activity and stretching will be undertaken. Dynamic concentric muscle strength for the 6 exercises undertaken in the program will be measured using the one repetition maximum (1-RM) method. The 1-RM is the maximal weight an individual can move through a full range of motion without change in body position other than that dictated by the specific exercise motion [26]. Muscle endurance will be assessed using the maximal number of repetitions performed at 70% of 1-RM for the chest press and leg press exercises (representing upper and lower body muscle endurance, respectively) [27].

##### Physical Function

A battery of tests will be used to assess functional performance [20,27]. Tests will be performed in triplicate (except for the 400-m walk which will be performed once) with sufficient recovery time between trials. The best performance on each test will be used in the analyses. The tests will be: 1) Repeated chair rise; 2) Stair climb; 3) 6-meter backward tandem walk; 4) 6-meter walk, usual and fast pace; and 5) 400-m walk.

##### Balance and Risk of Falling

A Neurocom Smart Balancemaster (Neurocom, OR, USA) will be used to assess static and dynamic balance. This device measures ground reaction force to track whole body centre of pressure and a tilting visual field and support platform to separate the visual, somatosensory and vestibular balance sense of the patient. During the course of the intervention, all participants will record any falls that take place and submit monthly fall records to the investigators.

##### Physical Activity, Quality of Life and Psychological Distress

Self-reported physical activity will be assessed by the leisure score index from the Godin Leisure-Time Exercise Questionnaire.

Health-related quality of life will be measured using the EORTC QLQ-C30 and EORTC QLQ-PR25 as well as a health history questionnaire [13,28]. This validated instrument is an integrated system to assess quality of life in cancer patients and has been extensively employed in clinical trials [29]. The Brief Symptom Inventory-18 (BSI-18) will be used to assess psychological distress (Anxiety, Depression and Somatisation) [30].

### Exercise Intervention

All three exercise groups: (1) resistance/impact-loading exercise; (2) resistance/cardiovascular exercise; and (3) usual care/delayed exercise will train 2 times per week in an exercise clinic. Weight machines will be used to ensure participant safety for those in the resistance/impact-loading exercise and the resistance/cardiovascular exercise groups. The clinic sessions will take approximately 60 minutes (this includes the warm-up and cool-down periods) and will be conducted in the Exercise Clinics at Edith Cowan University in Perth and at The University of Queensland in Brisbane. Sessions will commence with a 10-minute warm-up comprising low-level aerobic activities such as walking and stationary cycling, as well as stretching. The resistance training regimen (groups 1 and 2) will include 6 exercises that target the major upper and lower body muscle groups, which we have used previously in a number of studies [20,26,27,31-33]. The rest period between sets will be 1–2 minutes. To ensure the progressive nature of the training program, subjects will be encouraged to work past the specific repetition maximums (RMs) prescribed. The resistance will be increased by 5–10% increment for the next set/training session if subjects are able to perform more repetitions than the RMs specified during a set. Intensity will be manipulated from 6–12-RM (e.g. the maximal weight that can be lifted 6 to 12 times) using 1–4 sets per exercise.

The impact-loading regimen involves several activities which we have been previously used in a year-long training study in postmenopausal women [34]. For the first 12 weeks, 2 rotations will be performed of skipping (30 sec), bounding over soft hurdles (13–16 cm), and drop jumping (10–15 cm). In the second 12 weeks, hopping on one leg (10 times) will be added, and 3 rotations of all activities will be performed. In the third 12-week period, leaping (10 times) will replace skipping, and for the remainder of the program 4 rotations will be performed of bounding (19–25 cm), drop jumping (20–25 cm), hopping, and leaping. These activities result in substantial peak ground reaction forces ranging from 3.4 to 5.2 times body weight and are deemed to be safe and acceptable by older people and effective for increasing bone accretion [34].

All exercise sessions will be conducted in small groups of up to 10 participants, with participants exercising in pairs or under direct supervision to ensure correct technique and minimize the risk for injury. Each session will conclude with a 5-minute cool-down period of stretching activities.

In addition to the clinic training, twice weekly home-based training will take place. As with the clinic impact-loading program, the home exercise program will also follow a circuit routine and comprise, in a progressive fashion, 2 to 4 rotations of skipping, hopping, leaping, and drop jumping.

The usual care/delayed exercise group (group 3) will act as a control group for the resistance/cardiovascular group in the initial 6 months and for the resistance/impact loading intervention group for the full 12 months. Participants in this group will be provided with a printed booklet with information about exercise, and in the second 6-month period cycling (non impact) exercise sessions will be undertaken twice a week. Further, we will offer participants in this group a 3-month whole body resistance exercise program following the completion of the second 6-month period.

The resistance/cardiovascular exercise (group 2) will undertake the same resistance training regimen as described above for group (1) that will include 6 exercises that target the major upper and lower body muscle groups for the initial 6 months with a follow up home based program for the remaining 6 months of the program. In addition, each clinic session will include 20–30 minutes of aerobic exercise using various modes such as walking or jogging on a treadmill, cycling or rowing stationary ergometer, or exercising on a cross training machine. Target intensity will be 60%–85% of estimated maximum heart rate (calculated as 220 – age) with individual heart rate monitors (Polar Electra Oy, Finland) provided for each participant. In addition to the clinic training, patients from group 2 will be encouraged to undertake home-based training incorporating aerobic activity (e.g. walking, cycling) with the aim to accumulate at least 150 minutes per week for the duration of the study.

In order to reduce the possibility of boredom or overreaching the exercise program will be periodized by cycling emphasis on intensity and volume. Also, within sessions variations of circuit training and intermittent exercise sessions (intervals of high and low intensity exercise) will be used. The criteria for exercise program design will be optimal stimulus to the cardiorespiratory and neuromuscular systems while maximizing compliance and retention.

All participants will be asked to maintain customary physical activity and dietary patterns over the intervention period, and physical activity and dietary intake will be assessed at baseline, 6 months and 12 months. During the course of the study, participants will be required to maintain an activity log and record their recreational physical activities. Dietary intake, at the same time points as for physical activity, will be assessed using a 4-day dietary record. Dietary information will be derived using the FoodWorks software program. A summary of the training program for the three exercise groups is presented in Figure 2.

**Figure 2 F2:**
[figure not shown]
**Exercise interventions and timeline**.

### Calculation of Sample Size and Statistical Analysis

Data from our 20-week [20] and 36-week [28] preliminary studies in prostate cancer patients indicate that the standard deviation (SD) for change in our primary outcome of BMD equates to ~4.8%, 3.3%, and 2.5% for the hip, lumbar spine, and total body, respectively. With ADT, the annual loss is reported to be 2–8% at the spine and 1.8–6.5% at the hip [35], and based on our 36-week data, we obtain an annualized loss for the total body of 3.5%. However, loss in BMD is greatest in the first year of ADT [36], although continued losses are reported beyond this time period [36,37]. Consequently, as participants will have been on ADT for varying time periods and based on studies to date, we anticipate losses of ~3% and 2.5% at the clinically relevant fracture sites of the spine and hip, and 1.5% for the whole body. To be conservative, we anticipate that our resistance and impact-loading regimen will result in a modest increase of ~1%, whereas the active control regimen should have a negligible attenuating effect on BMD loss. Therefore, we anticipate a difference between the exercise and control groups of ~3.5% at the hip, 4.0% at the lumbar spine, and 2.5% for the whole body, which would be clearly clinically significant and substantially reduce the risk for fracture. To achieve 90% power at an alpha level of 0.05 (two-tailed), 40 subjects per group are required to demonstrate a difference between groups at each bone site at the end of the 12-month intervention. Regarding the second main comparison, the resistance training/aerobic group vs. the active control group for change in maximal exercise capacity as measured in metabolic equivalents (METS), 48 subjects per group are required to demonstrate a 0.66 SD difference between groups at the end of the 6-month intervention period and also potentially at 12-month follow-up [38,39]. Previous experience with exercise trials that we have conducted indicates an attrition rate of up to 25% over the course of the study period. However, to be conservative we will account for an attrition rate of up to 35%. Therefore, to adequately ensure that we have sufficient subject numbers at the end of the intervention, 65 subjects will be randomized to each of the three groups (N = 195). A sample size of 195 will also provide us with sufficient power to detect differences in our secondary outcomes.

Data will be analysed using the SPSS statistical software package. Analyses will include standard descriptive statistics, Student's t tests, correlation and regression, and two-way (group × time) repeated measures ANOVA to examine differences between groups over time. All tests will be two-tailed and an alpha level of 0.05 will be applied as the criterion for statistical significance.

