## Abstract

**Background:**

Androgen deprivation therapy (ADT) is accompanied by a number of adverse side effects including reduced bone mass and increased risk for fracture, reduced lean mass and muscle strength, mood disturbance and increased fat mass compromising physical functioning, independence, and quality of life. The purpose of this investigation is to examine the effects of long term exercise on reversing musculoskeletal-related side effects, and cardiovascular and diabetes risk factors in men receiving androgen deprivation for their prostate cancer. Specifically, we aim to investigate the effects of a 12-month exercise program designed to load the musculoskeletal system and reduce cardiovascular and diabetes disease progression on the following primary endpoints: 1) bone mineral density; 2) cardiorespiratory function and maximal oxygen capacity; 3) body composition (lean mass and fat mass); 4) blood pressure and cardiovascular function; 5) lipids and glycemic control; and 6) quality of life and psychological distress.

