**Discussion:**

The principal outcome of this project will be the determination of the strength of effect of exercise on the well established musculoskeletal, cardiovascular and insulin metabolism side effects of androgen deprivation in prostate cancer patients. As this project is much longer term than previous investigations in the area of exercise and cancer, we will gain knowledge as to the continuing effects of exercise in this patient population specifically targeting bone density, cardiovascular function, lean and fat mass, physical function and falls risk as primary study endpoints. In terms of advancement of prostate cancer care, we expect dissemination of the knowledge gained from this project to reduce fracture risk, improve physical and functional ability, quality of life and ultimately survival rate in this population.

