The purpose of this investigation is to examine the effects of long term exercise on reversing musculoskeletal-related side effects, and cardiovascular and diabetes risk factors in men receiving ADT for their prostate cancer. Specifically, we aim to investigate the effects of a 12-month exercise program designed to load the musculoskeletal system and reduce cardiovascular and diabetes disease progression on the following primary endpoints: 1) bone mineral density (BMD); 2) cardiorespiratory function and maximal oxygen capacity; 3) body composition (lean mass and fat mass); 4) blood pressure and cardiovascular function; and 5) lipids and glycemic control. Secondary endpoints will include: 1) physical and neuromuscular function; 2) balance and risk of falls; and 3) quality of life and psychological distress.

This project is unique as it utilizes impact-loading exercise in addition to resistance exercise as a means to counteract adverse musculoskeletal treatment related side effects (e.g. osteoporosis and sarcopenia) of ADT treated patients with prostate cancer. Further, this study also examines the effects of cardiorespiratory (aerobic) and resistance (anabolic) exercise as a means to counteract adverse body composition, cardiovascular and glucose metabolism co-morbidities related to treatment by ADT for patients with prostate cancer. Importantly, by comparing clinic versus home based exercise in one of the groups we will learn much about efficacy and feasibility of the home setting for more practical whole of patient population treatment. Finally, the extent to which anabolic versus aerobic exercise may ameliorate psychological distress and enhance quality of life will be assessed. This is the first study to our knowledge which is specifically designed to address all of these major side effects of ADT in a long term clinical trial.

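### An unadjusted 0.05 for every test, with three differing primary lists, puts the chance of a false-positive primary claim at about 10% to 19% even for the powered tests alone

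*Protocol article*

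**What the plan says.** The last paragraph of Calculation of Sample Size and Statistical Analysis fixes the level: "All tests will be two-tailed and an alpha level of 0.05 will be applied as the criterion for statistical significance". It makes no distinction between primary and other tests.

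The primary endpoints are listed differently in three places:
- **Abstract, Background:** six domains, ending with "5) lipids and glycemic control; and 6) quality of life and psychological distress".
- **Main text, Background:** five domains, ending with "4) blood pressure and cardiovascular function; and 5) lipids and glycemic control". Quality of life and distress are secondary here.
- **Abstract, Discussion:** a third list, "specifically targeting bone density, cardiovascular function, lean and fat mass, physical function and falls risk as primary study endpoints". The main-text Background classes physical function and falls risk as secondary.

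The sample size text is narrower. It gives the SD of "change in our primary outcome of BMD equates to ~4.8%, 3.3%, and 2.5% for the hip, lumbar spine, and total body, respectively", and differences to detect of "3.5% at the hip, 4.0% at the lumbar spine, and 2.5% for the whole body", with 40 men per group for 90% power at each site at two-sided 0.05. It then adds: "Regarding the second main comparison, the resistance training/aerobic group vs. the active control group for change in maximal exercise capacity", with 48 per group for a 0.66 SD difference at 6 months.

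**The concern.** With one flat level and no settled primary list, a positive result on any listed primary endpoint could be reported as a primary finding of a phase III trial at nominal 0.05. The article says that its most important outcome will be clinical guidelines for exercise in men on androgen deprivation, so the error rate across those primary claims matters. An analysis plan that controlled it would have to depart from the stated rule, so this is not a detail left open for that plan to fill in.

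**Working it through.** **1. Is any alpha reserved in the sample size?** Inputs are the SDs and differences quoted above, 90% power and two-sided 0.05. The article does not repeat the power for METS, so 90% is assumed there.

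n per group = 2 × (1.960 + 1.282)² × (SD / difference)², where (1.960 + 1.282)² = 10.51.

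| Test | SD / difference | n per group | Stated |
|---|---|---|---|
| Hip BMD | 4.8 / 3.5 | 39.5, so 40 | 40 |
| Spine BMD | 3.3 / 4.0 | 14.3, so 15 | covered by 40 |
| Whole-body BMD | 2.5 / 2.5 | 21.0, so 22 | covered by 40 |
| METS | 1 / 0.66 | 48.2 | 48 |

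Both stated figures reproduce with the full 0.05, and the hip drives the 40. At 0.025 the same formula gives 47 (hip) and 57 (METS). No alpha has been split between the two main comparisons or among the bone sites.

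**2. Chance of at least one false positive.** For k independent tests with no true effects it is 1 − 0.95^k.

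| Family | k | Chance |
|---|---|---|
| Two main tests (one bone site, METS) | 2 | 9.8% |
| Four powered tests (three bone sites, METS) | 4 | 18.5% |
| Five domains, one comparison | 5 | 22.6% |
| Six domains, one comparison | 6 | 26.5% |
| Six domains, two comparisons | 12 | 46.0% |

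**3. Effect of correlation.** The article gives no correlations between endpoints, so a range is assumed. A simulation (200,000 runs, no true effects, equal correlation between endpoints, both exercise arms compared with the same control arm) gave, for six domains and two comparisons, 40% at correlation 0.3, 35% at 0.5 and 28% at 0.7.

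**4. Power if the two lead tests share 0.05.** The first Holm step is 0.05 / 2 = 0.025. Evaluable men per arm after the article's 35% attrition: 65 × 0.65 = 42. Two-sample t test power:

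| Test | n per arm | At 0.05 | At 0.025 |
|---|---|---|---|
| Hip BMD | 42 | 91% | 85% |
| METS | 42 | 85% | 77% |
| METS | 48 | 89% | 83% |

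Part of the 77% for METS comes from attrition (42 rather than 48 men), not from the split of alpha.

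**The case against.** **This is a condensed article, and multiplicity is usually settled in the analysis plan.** Silence on the subject would be no finding. But the article is not silent: it states one level for all tests, and its primary lists contradict each other.

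**The sample size text already implies a hierarchy.** It calls BMD the primary outcome and names one further main comparison. The two concern different regimens, and whether to adjust across separate arm-specific questions is debated. That is a fair point, and it is why 10% to 19% is the leading figure here. It does not cover three bone sites within one comparison, and the text does not say that BMD alone carries the confirmatory claim.

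**A reader might infer much more.** Counting every measurement under Primary Study Endpoints gives roughly 21 to 31 variables. Taking 27 in two comparisons gives 1 − 0.95^54 = 94%, and suggests that a false-positive primary result is likely. The documents do not support that:
- The count appears nowhere in the article, and being measured under a heading does not make a variable a primary hypothesis. The marker list beginning "Testosterone, prostate specific antigen (PSA), insulin, lipid profile, glucose" includes items such as testosterone, PSA and C-reactive protein that are neither lipid nor glycemic measures.
- The body-composition variables overlap mechanically, so independence fails badly for them.
- Two comparisons at two visits is not a uniform multiplier. Under Exercise Intervention, group 3 is the control for group 2 only in the first 6 months, and the sample size text adds month 12 for METS only as a possibility. The planned group × time ANOVA can also test arms and visits jointly.

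Nor is it right that the plan controls no error rate: the per-test rate is 5%. What is not controlled is the rate across the primary claims.

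**Conclusion.** The point holds in limited form. The article fixes 0.05 for every test, does not settle which endpoints are primary, and powers four tests at the full level. On the narrowest reading, the chance of at least one false-positive primary claim is about two to four times the nominal 5%. It is higher if each listed domain carries one primary test, but stays below one half even for six domains in two comparisons. These figures assume no true effect on any endpoint. The 10%, 19% and 46% also assume independence, and the 28% to 40% range rests on assumed correlations. The trial is not invalidated; the gap is in its confirmatory claims and can be closed cheaply.

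**What to change.** 1. Give one primary list and use it in the abstract, the aims, the endpoint headings and the sample size section.
2. Limit confirmatory testing to the comparisons already powered: BMD at month 12 (group 1 vs 3) and METS at month 6 (group 2 vs 3), by Holm at overall two-sided 0.05.
3. Name one lead bone site in advance. The hip is a natural example because it drives the 40 per group, though the documents do not dictate it and it is the site with least power. Put the other two sites in a fixed order after it.
4. State the alpha for those two sites so that none is spent twice. One option is to test them at the 0.025 of the BMD branch, with METS moving up to 0.05 only once the whole bone sequence has succeeded. The other is to test them only after both lead tests have succeeded, at 0.05.
5. Restrict the flat 0.05 sentence accordingly, and report all other variables with confidence intervals and no confirmatory claim.

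Cost: wording, plus a restated power. At the first Holm step the loss is about 6 points for hip BMD and 8 for METS at 42 per arm, or 6 for METS at 48. If either lead test succeeds, Holm can return the other to 0.05, subject to item 4. Restoring 90% power at 0.025 would take about 47 (hip) and 57 (METS) evaluable men per group. No extra enrolment is proposed; the lower power should simply be stated.
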